#### Study design

The study is a cluster-randomized, non-inferiority trial with secondary schools as the unit of randomization. It is designed as a Hybrid Trial Type 2 Effectiveness-Implementation study [10] to answer two key overarching policy-relevant questions: 1) Do either of the CyberRwanda versions (self-service, facilitated) improve the health and wellbeing of youth compared to schools without access to CyberRwanda? and 2) If one or more of the CyberRwanda versions is found to be effective, is the self-service version at least as effective, within a specified margin, as the facilitated version?

In addition to rigorously measuring the impact of CyberRwanda, we will also include data collection beyond the primary outcomes to learn about acceptability, feasibility, and implementation successes and challenges. This will enable the team at the conclusion of the study to understand not only whether CyberRwanda worked, but why and in what context.

The impact evaluation will use an experimental approach embedded in Proctor’s implementation science framework [15]. Should CyberRwanda be found to be effective, the implementation science framework will allow us to determine potential barriers and facilitators to scale-up and sustainability through input from stakeholders at multiple levels: the individual level (students, peer facilitators, parents, and teachers), the organizational level (schools) and the policy level (community leaders, government officials).

#### Study arms

There are three study arms: 1) CyberRwanda self-service; 2) CyberRwanda facilitated; and 3) control schools, which will receive the standard services that are available in the community. The difference between the self-service and facilitated models is outlined in the section on the CyberRwanda school implementation model, above. Following the end of the evaluation, CyberRwanda will be scaled nationally and made available to control schools.

#### Study population and eligibility criteria

We will recruit 60 schools in 8 districts in Rwanda, randomly selected from a sampling frame of schools in these districts. The study districts are Gatsibo, Nyagatare, Kayonza, Huye, Gasabo, Bugesera, Nyarugenge and Rwamagana. Eligible schools will meet the following criteria:
Willing to participate (as determined by school leadership)Within 4.5 km of a participating pharmacyAt least 1.5 km from another secondary school to reduce unintended spillover effectsA minimum of 150 students attending the schoolDay schools only (no boarding or mixed schools).

Within participating schools, irrespective of the study arm, we will recruit all students enrolled in levels S1 and S2 (secondary school grades 1 and 2) at baseline to enroll in the evaluation cohort. Late entry to school and repetition of levels leads to age variation within levels in Rwanda [16]. Data from the pilot study showed this range of levels will yield the most students within the target age group. Eligibility criteria for students is as follows:
Attending a study school at baselineBetween 12 and 19 years of ageConsent (for participants ages 18–19) or assent (for participants under 18) provided to participateParental consent provided (for participants under 18)Willingness to provide valid contact information for study follow-up purposes.

#### Randomization

Randomization will occur at the cluster (school) level, stratified by district. There is no concealment at the cluster level, but individual participants in the control schools will not be explicitly told about the intervention. The study is not blinded.

Society for Family Health Rwanda (SFH) is responsible for recruiting schools into the study pool and inviting them to join a district meeting. The YLabs team will support a participatory randomization process at the district meeting. All schools that agree to participate will move forward to the randomization process (data on the proportion of schools who are approached and who subsequently refuse participation will be recorded). At each district meeting, we will ask each school representative to choose a ball out of a bag for their district. Color coded balls will represent which arm of the study the school will be randomly allocated: control, CyberRwanda self-service, or CyberRwanda facilitated. Participants will not see the color of the ball that they draw from the bag, nor will they know the significance of the color until all the balls have been drawn.

The head teacher at the participating schools provides consent for their school to be included within the study. This is agreed before knowing which arm (control or either treatment) the school will receive. Consent is provided by participating students if over 18 years old. Students under 18 provide assent and consent from their parents. Parental consent forms will be distributed at school to all students in S1 and S2 in study schools. Students will be instructed to bring the consent forms home to parents/guardians, ask them to read and sign them, and bring them back to school within the next week. Study staff will return 1 week after distributing consent forms to collect signed parental consent forms for students, and record parental consent status for each student. Request for withdrawal from the study by any individual participant or school is respected and enabled. Model consent forms can be found in Additional file 4.

#### Sample size calculations

The sample size was determined for the primary outcome of uptake of a modern contraceptive method. Power and sample size analyses were conducted for the primary analysis using 2000 simulated datasets (created in R statistical software) constructed based on historic data on the proportion of sexually active youth currently using a modern contraceptive method.

The primary analysis is powered at 80% to detect the presence of an intervention effect when CyberRwanda facilitated has a relative risk of at least 2.5. Although this relative risk seems large, in absolute terms, the baseline percentage of girls using contraception is only 2%, so this would mean increasing that to 5%. To achieve this power, we need to enroll 60 schools and 50 girls per school (equal cluster size is assumed). When we include boys (who are not part of the primary outcome on which the study is powered), this means we will enroll a total of 100 students per school, for a total of 6000 students in the study.

#### SPIRIT diagram

The SPIRIT flow diagram for this trial is included in Fig. 5, and completed checklist included in Additional file 3.

**Fig. 5 Fig5:**
[figure not shown]
Cluster Randomized Hybrid Effectiveness-Implementation Trial Study Design. Schematic of the study design

#### Data collection

Study participants will be asked to complete three surveys at three different time points during the study: one at baseline, one at midline (9–12 months after launch), and one at the end of the study (after 24 months). Surveys will be administered in Kinyarwanda using a tablet computer and Qualtrics offline survey software and will take 30–45 min to complete. The survey will cover the following broad topic areas: sociodemographic characteristics, knowledge about FP/RH, social norms related to sexual health, gender roles, norms related to gender-based violence, intentions related to having a family, use of contraceptives, communication with partners, sexual behavior, childbearing, future aspirations and goal-setting, and attitudes and intentions toward school and employment (see draft baseline questionnaire in Additional file 2).

In addition to the surveys, continuous, real-time data will be collected using Google Analytics to understand user engagement patterns (e.g. drop-off points in character storylines, online ordering behaviors) in all three arms.

As preparation for implementation, we conducted an eight-week pilot study in September to October 2019 in 4 schools and 2 youth centers in Nyagatare and Kigali (Nyarugenge and Gasabo districts), to refine the implementation model and data collection instruments.

Data will be strictly managed and stored securely to maintain participant confidentiality and minimize the risk of potential harms such as accidental disclosure. Study Investigators as specified in the IRB documents will have access to the final study dataset. Full details of data management and monitoring protocols can be found in Additional file 5.

#### Student follow-up

The impact evaluation carries a high risk of attrition as we are enrolling a cohort of students at baseline and will assess outcomes 24 months later. We can expect that over the 2 years of the impact study between 5 and 20% of students will drop out of school, and girls are more likely to be out of school than boys from age 15 and up [16]. Efforts to retain members of each cohort – even if they leave school – will be crucial given that reasons for dropping out of school are closely related to our primary outcomes (i.e. childbearing), and any significant differential attrition between study arms will bias results. We will mitigate the risk of study dropout by collecting multiple modes of contact for each enrolled student and parents at baseline, as well as providing participants small communication payments (<$1 USD) for regularly updating contact information every school term so we can retain updated contact information. In addition to these efforts, we have also built in to our power calculations that we can expect a 10% attrition rate over the course of the study.

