#### Outcomes

The primary outcomes, measured at the individual participant level, are:
Uptake of a modern method of contraception (ages 15–19): The proportion of youth who report currently using a modern method of contraception at endline (24 months)Initiation of childbearing (ages 15–19): The proportion of youth who report having ever been pregnant or fathered a pregnancy at endline (24 months), regardless of the pregnancy outcomeHIV testing (ages 12–19): The proportion of youth who have ever had an HIV test at endline (24 months).

While the intervention will be available to 12–19-year-olds at study intervention schools, the first two primary outcomes are measured for 15–19-year-olds for two main reasons: 1) sample size would need to be increased substantially to have sufficient statistical power to detect an effect in the younger age group; and 2) stakeholders were more comfortable focusing the evaluation outcomes on older adolescents to align with social expectations on talking about sexuality. HIV testing is not as stigmatized according to age, because it is routinely conducted irrespective of sexual activity.

Secondary outcomes include the following, measured at the individual participant level for participants aged 15–19 at endline (24 months):
Level of knowledge of contraceptive methods and how to prevent pregnancyBehavioral intentions to use contraceptives, pregnancy intentions, intent to discuss contraceptives with partnerSelf-efficacy related to family planning and reproductive healthSocial norms related to contraceptive use and other reproductive health behaviorsEngagement in employment, education and training: proportion of youth currently in school, training or employment.

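### Childbearing is an irreversible 'ever' outcome but is defined by the endline report alone, so a pregnancy reported at midline by a student later lost does not count

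*Protocol article*

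**What the plan says.** All references are to Phase 2 of the protocol article.

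- **Outcomes.** Childbearing, a primary outcome for ages 15–19, is "The proportion of youth who report having ever been pregnant or fathered a pregnancy at endline (24 months"), whatever the pregnancy outcome. The reporting itself is placed at endline.
- **Data collection.** Participants are asked to complete three surveys: "one at baseline, one at midline (9–12 months after launch), and one at the end of the study (after 24 months"). The listed topics include "use of contraceptives, communication with partners, sexual behavior, childbearing, future aspirations and goal-setting".
- **Student follow-up.** The authors expect that "between 5 and 20% of students will drop out of school" over two years, say that "reasons for dropping out of school are closely related to our primary outcomes (i.e. childbearing"), and state that "any significant differential attrition between study arms will bias results". Their response is retention work (several contact routes, small payments each term, continued follow-up of school leavers) and a 10% attrition allowance in the power calculation.
- **Data analysis.** Childbearing enters a generalized linear mixed model (GLMM) as one binary outcome. The section does not mention midline reports or missing outcomes.

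**The concern.** A student who reports a pregnancy at midline has a known 24-month status, whatever happens to her afterwards. The definition nevertheless requires a report at endline, so if she cannot be found then, her known event does not enter the primary outcome. The protocol identifies the mechanism that makes this matter: childbearing is linked to leaving school, and school leavers are harder to trace.

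Two consequences should be kept apart. If students with the event are lost more often than others, the observed risk is too low in every arm. If the extra loss differs between arms, the comparison is biased as well, in either direction. The 10% allowance protects power and does nothing about either bias.

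**Working it through.** **The plan's own figures.** The article gives no childbearing rate, no loss by event status and no share of events occurring by midline. Its sample-size arithmetic is consistent (60 × 50 = 3000 girls, 60 × 100 = 6000 students, 2% × 2.5 = 5%), but it concerns contraceptive uptake and is not disputed here. The only figure used from the document is the 10% attrition, as a check that total loss looks realistic. All other inputs are assumptions.

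**Notation, per arm.** p = true 24-month risk; q1 = loss at endline among students with the event; q0 = loss among the rest; s = share of events already reported at midline, with midline assumed complete.

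- Endline only: p(1−q1) / [p(1−q1) + (1−p)(1−q0)]
- Midline positives counted, other lost students imputed from midline status: ps + (1−ps) × h, where h = p(1−s)(1−q1) / [p(1−s)(1−q1) + (1−p)(1−q0)]. This is the large-sample result of the fix without further covariates.

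**Case A: true risk 10% in both arms, q0 = 8%, q1 = 40% control and 20% intervention, s = 0.5.**

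- Total loss: 0.04 + 0.072 = 11.2% and 0.02 + 0.072 = 9.2%, close to the planned 10%.
- Endline only: 0.060/0.888 = 6.8% and 0.080/0.908 = 8.8%. RR 1.30; truth 1.00.
- With midline: 0.05 + 0.95 × (0.03/0.858) = 8.3% and 0.05 + 0.95 × (0.04/0.868) = 9.4%. RR 1.13.

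**Case B: true risk 5% control and 3.5% intervention (RR 0.70), q0 = 9%, s = 0.3 to 0.5.**

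| q1 control / intervention | Endline-only risks | Endline-only RR | RR with midline and imputation |
|---|---|---|---|
| 30% / 30% | 0.035/0.8995 = 3.9%; 0.0245/0.90265 = 2.7% | 0.70 | 0.70 |
| 30% / 20% | 3.9%; 0.028/0.90615 = 3.1% | 0.79 | 0.74–0.76 |
| 50% / 30% | 0.025/0.8895 = 2.8%; 2.7% | 0.97 | 0.80–0.85 |

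Total loss in these rows is between 9% and 11% in each arm, so overall attrition would not reveal the problem. One entry in full (30% / 20%, s = 0.5): control 0.025 + 0.975 × (0.0175/0.882) = 4.43%; intervention 0.0175 + 0.9825 × (0.014/0.89215) = 3.29%; RR 0.74.

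In the equal-loss row the relative risk is essentially unaffected, but the control risk reads 3.9% against a true 5%. Using midline raises it to 4.2–4.4%.

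**Why counting midline positives alone is not enough.** Take q1 = 10% in both arms, so that loss is almost unrelated to the event. Adding midline-positive lost students while dropping the other lost students gives a control risk of (0.045 + 0.05 × 0.10 × s) / (0.045 + 0.05 × 0.10 × s + 0.8645). This is 5.1% at s = 0.3 and 5.2% at s = 0.5, above the true 5%. With imputation and s = 0.5 it is 0.025 + 0.975 × (0.0225/0.887) = 4.97%.

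**The case against.** The strongest defence is that the Outcomes section only fixes a time point, that the article nowhere says midline reports are thrown away, and that missing-outcome handling normally sits in an analysis plan not shown here. Much of this stands. A reader might infer a decision to discard midline data, but the text supports only the narrower statement that the definition, as worded, leaves such a report out. The absence of a missing-data method is not the complaint. The definition is, because the protocol does fix it.

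Other stronger readings also fail:

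- **HIV testing.** It is likewise an 'ever' outcome ("The proportion of youth who have ever had an HIV test at endline (24 months")), so a reader might include it. But the topic list does not name HIV testing, and no link between it and drop-out is stated.
- **School drop-out as study loss.** The stated link is to leaving school, and leavers are to be followed. Higher study loss among students with the event is plausible, not documented.
- **Midline known for everyone.** Students are asked to complete it, and early leavers may miss it. The article also does not show whether students under 15 answer the childbearing item at midline.
- **Need for a new primary model.** A discrete-time model is unnecessary. Imputation works within the planned GLMM and leaves the non-inferiority step intact.

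It is also fair that the event is irreversible but the self-report is not. The Discussion acknowledges misreporting, and a false midline yes would become permanent.

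**Conclusion.** The point holds for childbearing and should be addressed. The definition omits information that the trial plans to collect on an irreversible event, in the setting where the protocol itself expects informative drop-out.

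The illustrations are not forecasts. Material bias in the relative risk needs loss among students with the event to differ between arms, and the article gives no figure for that. With equal loss the relative risk barely moves and only the absolute risk is understated (3.9% against 5% at 30% loss). With unequal loss, a true 0.70 can read as 0.79 or 0.97, and a true 1.00 as 1.30. Midline data recover part of this: 0.74–0.76, 0.80–0.85 and 1.13 respectively, given complete midline and 30–50% of events by then (50% for the 1.13). Bias from events after midline in lost students remains.

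**What to change.** 1. Define initiation of childbearing as ever having been pregnant or fathered a pregnancy by 24 months, with a positive midline report counting as positive.
2. Keep the planned GLMM. For the remaining students without an endline report, multiply impute 24-month status from midline and baseline status, arm, age, sex and school. Do not simply add the midline positives, which biases the risk upwards.
3. Report the endline-only analysis as a sensitivity analysis. It also shows how far inconsistent self-reports matter.
4. Apply the same rule to HIV testing only if the midline questionnaire asks about it.

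The cost is a change of outcome wording and modest extra analysis, with no new fieldwork for childbearing. The drawbacks are that a false midline yes would count and that bias from events after midline in lost students is not removed.

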#### Data analysis

To first assess the presence of an intervention effect, we will utilize a generalized linear mixed model (GLMM) with uptake of a modern contraceptive method (binary outcome) and initiation of childbearing (binary outcome) as the outcome variables. The model will include a binary explanatory variable for the intervention group (control vs. CyberRwanda in either the self-service or facilitated arm) with control group as the reference, and model terms for the stratification factor (district) as well as other relevant variables measured at baseline (e.g. age, sex). We will present relative risks and 95% confidence intervals using robust standard errors to account for clustering at the school and district levels.

If there is evidence of a statistically significant intervention effect relative to control, we will proceed with the assessment of non-inferiority to understand whether CyberRwanda self-service is non-inferior to CyberRwanda facilitated within a specified margin. To do this, the coefficients on the categorical variable for the intervention groups can be used as approximations of the log relative risks (RRs) comparing the probability of contraceptive uptake (or initiation of childbearing) in the intervention arms compared to control arm. We will use a one-sided Wald-style test of non-inferiority, based on an a priori specified non-inferiority margin of 50% of the lower bound of the confidence interval for CyberRwanda facilitated.

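### The pooled effect opens the non-inferiority test without requiring a facilitated effect, on which its margin depends; the 80% power also rests on an unstated self-service effect

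*Protocol article*

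**What the plan says.** All places are in Phase 2 of the protocol article.

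- **Question 1 (Study design):** "Do either of the CyberRwanda versions (self-service, facilitated) improve the health and wellbeing of youth compared to schools without access to CyberRwanda". Question 2 follows on a condition: "If one or more of the CyberRwanda versions is found to be effective, is the self-service version at least as effective" as facilitated, within a margin.
- **Effectiveness model (Data analysis):** one two-level term. "The model will include a binary explanatory variable for the intervention group (control vs. CyberRwanda in either the self-service or facilitated arm").
- **Gate (Data analysis):** "If there is evidence of a statistically significant intervention effect relative to control, we will proceed with the assessment of non-inferiority". Read in sequence, the effect meant is the pooled one from that model.
- **Arm-specific estimates (Data analysis):** these appear only after the gate, as inputs to the non-inferiority test: "the coefficients on the categorical variable for the intervention groups can be used as approximations of the log relative risks (RRs"). No test of either arm against control is stated.
- **Margin (Data analysis):** a "non-inferiority margin of 50% of the lower bound of the confidence interval for CyberRwanda facilitated". The scale of that bound, log RR or RR, is not given.
- **Power (Sample size calculations):** the main comparison is described as "powered at 80% to detect the presence of an intervention effect when CyberRwanda facilitated has a relative risk of at least 2.5", that is, 2% rising to 5% among girls, with 60 schools and 50 girls per school. The self-service effect in the simulations is not given.

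**The concern.** Three parts of the plan rest on different quantities. The gate depends on the average of the two active arms. The margin depends on the facilitated arm alone. The power statement names only the facilitated effect but applies to a test of the average.

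The gate matters most. A margin set as a fraction of the comparator's lower bound makes sense only if that bound lies on the beneficial side of no effect. The pooled test has twice as many active schools as the facilitated comparison, so it can be significant when facilitated versus control is not. Self-service could then be declared non-inferior to a comparator that this trial has not shown to work. The condition in Study design does not close the gap either, because one or more effective versions could mean self-service alone.

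The power statement matters for planning. If self-service is weak, averaging dilutes a real facilitated effect and the primary test can miss it. A positive pooled result does not say which version works, and a null one does not show that neither works.

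**Working it through.** **Inputs.** From Sample size calculations: control 2%, facilitated 5%, 60 schools, 50 girls per school. From Student follow-up: 10% attrition, so 50 × 0.9 = 45 girls per school. From Data analysis: 95% intervals, read as two-sided 5%. **Assumed:** 1:1:1 allocation (20 schools per arm, so 20 against 40 in the pooled test) and ICC 0 to 0.02. The article states neither.

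**1. The plan's 80%.** The check uses the usual two-proportion formula, with n divided by the design effect 1 + (m − 1) × ICC. It returns 80% for the pooled test with both arms at RR 2.5 if ICC is about 0.021–0.024. It also returns 80% for facilitated versus control alone if ICC is about 0.012–0.014. The figure is attainable but cannot be tied to one scenario. That is not in itself an error.

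**2. Pooled power with self-service inert, most favourable case (ICC 0, no attrition).**
- n₁ = 20 × 50 = 1000 and n₂ = 2000
- p₁ = 0.02 and p₂ = (0.05 + 0.02)/2 = 0.035, so d = 0.015
- p̄ = (1000 × 0.02 + 2000 × 0.035)/3000 = 0.03
- SE₀ = √[0.03 × 0.97 × (1/1000 + 1/2000)] = 0.00661
- SE₁ = √[0.02 × 0.98/1000 + 0.035 × 0.965/2000] = 0.00604
- Power = Φ[(0.015 − 1.96 × 0.00661)/0.00604] = Φ(0.34) = 63%

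A log-RR Wald test gives 61%, unpooled variance 70%, and a one-sided 5% test 75%. None reaches 80%. With 45 girls the formula gives 58%. At ICC 0.02 the design effect is 1 + 44 × 0.02 = 1.88, the effective n₁ is 900/1.88 = 479, and power is 33%.

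**3. Smallest self-service RR that keeps pooled power at 80%** (facilitated 2.5, 45 girls, same formula):

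| ICC | Self-service RR needed |
|---|---|
| 0 | 1.49 |
| 0.005 | 1.74 |
| 0.01 | 1.98 |
| 0.02 | 2.44 |

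**4. Simulation of the gate.** Beta-binomial data, 20 schools per arm, 45 girls per school, school-level Welch tests, 40,000 trials per scenario. Gate failure means that the pooled test is significant while facilitated versus control is not.

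| Facilitated RR / self-service RR | Result | ICC 0 | ICC 0.01 | ICC 0.02 |
|---|---|---|---|---|
| 2.5 / 2.5 | gate failure | 6% | 12% | 15–16% |
| 2.0 / 2.0 | gate failure | 17% | 19% | 19% |
| 2.5 / 1.0 | pooled power | 59% | 47% | 41% |
| 2.5 / 1.0 | facilitated significant, pooled not | 34% | 35% | 31% |

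The 15–16% is the spread between repeat runs. The simulated power for an inert self-service arm is somewhat above the formula's 33–58% because the variance is handled differently. Neither is the planned mixed model, so both serve as a range.

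**5. The margin when the gate fails.** Let L be the facilitated lower bound, with L ≤ 1. On the log scale the margin is 0.5 × ln L ≤ 0, which is zero or negative. On the RR scale it is 0.5 × L, for example 0.5 × 1 = 0.5. That is a positive number, but it corresponds to no preserved effect.

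**The case against.** The other side has a good case on several points.

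- **Pooling matches some stated aims.** The Abstract and Background speak of the overall effectiveness of the programme, and Aims asks about CyberRwanda as a whole. A reader might infer that the pooled test cannot answer question 1. The text does not support that: a significant positive pooled effect shows that at least one version works.
- **Equal efficacy is not needed for 80%.** A reader might infer that the power claim fails unless self-service works as well as facilitated. Step 3 shows otherwise for ICC 0.01 or below. The simulated self-service effect and the ICC may also be recorded in the full protocol or analysis plan.
- **The worst gate scenario is implausible.** With facilitated inert and self-service at RR 2.5, the gate fails in 38–57% of simulated trials. But the facilitated model includes every self-service component plus peer clubs, so that ordering is the least likely. With facilitated at 2.5 and self-service between 1.0 and 2.0, failure occurs in 0% to about 9% of trials.
- **The margin does not always vanish.** It is zero or negative only on the log scale. The log-RR coefficients make that scale plausible, but the text does not fix it.
- **Pooled first, then each arm at 5%, is a valid closed procedure for two arms.**

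These points limit the size of the concern. They do not supply the missing condition on facilitated, and they do not make a power statement conditional on one arm true for a test of two. The closed-procedure defence would hold if the arm-versus-control tests were stated, but they are not.

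**Conclusion.** The point holds in a limited form.

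**Gate.** The rule lets non-inferiority be tested without a shown facilitated effect, while the margin is built from that arm's bound. Under the assumed allocation and ICC 0–0.02, this occurs in about 6–16% of trials with both arms at RR 2.5 and 17–19% with both at 2.0. The defect follows from the text; only its frequency depends on the assumptions.

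**Power.** The 80% cannot hold for the pooled test on the facilitated RR alone. With an inert self-service arm it is about 41–59% in simulation, and 63% by the standard formula even without clustering or attrition. A moderately weaker self-service arm (RR about 1.5–2.0) can still leave 80% at ICC 0.01 or less.

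**Interpretation.** The pooled test answers whether at least one version works only when it is positive. It does not identify which, and a null result does not rule out an effective version.

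A reader might go further and conclude that the pooled primary test must be replaced. The figures do not support that: the choice is a trade-off, set out under the fix.

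**What to change.** 1. **Gate.** Test non-inferiority only if facilitated versus control is itself significant, in the beneficial direction, in the three-level model. For contraceptive uptake this puts the 95% lower bound above 1, so a log-scale margin is positive. State the scale of the margin at the same time.
2. **Power.** Restate the 80% as conditional on the self-service RR and ICC used in the simulations, or rerun them over a range of both.
3. **Estimand and arm-specific tests.** Either declare the pooled contrast as the primary estimand, followed by stated tests of each arm against control at 5% (a valid closed procedure for two arms), or test each arm against control with multiplicity control.

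**Cost.** Items 1 and 2 need wording and, at most, a rerun of existing simulations. With the new gate, non-inferiority is tested less often. With both arms at RR 2.5, the trials lost are the 6–16% in which no shown effect supports the margin.

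Item 3 is a choice. In the same simulation with both arms at RR 2.5, replacing the pooled test with Holm lowers the chance of any positive result from 98% to 96%, 93% to 86% and 86% to 75% at ICC 0, 0.01 and 0.02, a loss of about 2–11 points. The two are about level (60% each) at self-service RR 1.5 and ICC 0.02. Holm clearly gains when one arm is nearly inert (about 60% against 41% at ICC 0.02).

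### Read literally, the robust standard errors rest on 8 districts rather than the 60 randomised schools, so the analysis is either anti-conservative or loses precision, depending on a correction the article does not state

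*Protocol article*

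**What the plan says.** All places are in the protocol article, Phase 2.

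- Study population and eligibility criteria: "We will recruit 60 schools in 8 districts in Rwanda".
- Randomization: "Randomization will occur at the cluster (school) level, stratified by district". District is therefore a stratum and school is the randomised unit.
- Data analysis: a generalized linear mixed model for contraceptive uptake and for initiation of childbearing. It has one binary term for control against both CyberRwanda arms pooled, terms for district as the stratification factor, and baseline covariates. The next sentence reads "We will present relative risks and 95% confidence intervals" "using robust standard errors to account for clustering at the school and district levels".
- The only test whose form is named is the later step: "We will use a one-sided Wald-style test of non-inferiority". No reference distribution, degrees of freedom or finite-sample correction is given for the primary intervals.
- Sample size calculations: "The primary analysis is powered at 80% to detect the presence of an intervention effect", with 60 schools and 50 girls per school, 2% against 5%, and no intraclass correlation given.

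**The concern.** A sandwich variance treats the highest clustering level as its set of independent units. Every school lies wholly within one district, so robust errors covering both levels reduce algebraically to errors clustered on district, which leaves 8 units. With so few, the sandwich is biased low and a normal critical value is too small for about 7 degrees of freedom.

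The design does not call for this. Arms are allocated to schools within districts, and differences between districts are absorbed by the district terms. The correlation that matters for the treatment contrast is the one within schools, and there are 60 of those.

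At stake are the intervals for the pooled effectiveness comparison and the significance gate that opens the non-inferiority assessment. If the same errors are used for the facilitated arm, the confidence bound that defines the non-inferiority margin is also affected.

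**Working it through.** **Inputs from the article.** 60 schools; 8 districts; schools randomised within district; district terms in the model; pooled contrast (about 40 against 20 schools); 95% intervals; 50 girls per school; 2% against 5%; 10% attrition (Student follow-up).

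**Assumed, because not given.** Intraclass correlation 0.01-0.05; outcome rates from 2% up to 30-40%; roughly equal or unequal numbers of schools per district; a marginal log-link Poisson model standing in for the mixed model.

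**1. The plan's own figure.** The only computed design figure is 80% power. For 2% against 5%, two-sided 5%, the usual two-proportion formula needs 588 individuals per arm. With 20 schools of 50 girls per arm, 1000/588 = 1.70 = 1 + 49 × ICC, so ICC = 0.014. After 10% attrition, 900/588 = 1.53 = 1 + 44 × ICC, so ICC = 0.012. For 40 against 20 schools the corresponding values are 0.024 and 0.021. The 80% is thus compatible with the inputs but can be neither confirmed nor refuted. These values lie inside the range simulated below.

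**2. Approximate error rate with 8 clusters.** Treat the district-clustered statistic as t on G - 1 = 7 degrees of freedom.
- With the G/(G-1) factor and a normal critical value: P(|t₇| > 1.96) = 9.1%.
- Without the factor the standard error is smaller by √(7/8): P(|t₇| > 1.96 × √(7/8)) = 10.9%.

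**3. Simulation under no effect.** 60 schools in 8 districts, pooled contrast, district terms in the model. Columns A and B are two layouts. A: 7-8 schools per district, rates 2-40%, ICC 0.01-0.05, 6,000 datasets per scenario, of which 5,198-6,000 were usable at the lowest rates. B: 1:1:1 within district, 45 girls per school, rate 2%, ICC 0.012 and 0.02, equal and unequal districts, 10,000 datasets per scenario.

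| Variance and reference | A | B |
|---|---|---|
| District, no correction, z | 10.4-11.9% | 11.8-13.6% |
| District, G/(G-1), z | 8.7-9.7% | 9.8-11.5% |
| District, G/(G-1), t(7) | not run | 5.4-6.4% |
| School, no correction, z | about 8-9% | 8.4-9.1% |
| School, corrected, t | 4.9-5.5% | 5.6-6.0% |

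A further run gave 10.9-11.6% and 8.8-9.5% for the first two rows, 4.5-5.4% for the third and 8-8.5% for the fourth. Widening layout B to rates of 2% and 30%, ICC 0.01 and 0.05, and models with and without district terms (2,500 datasets per scenario) spread the first three rows to 10.0-15.2%, 8.4-13.5% and 4.4-8.2%. With district terms, the last row spread to 4.7-7.1%.

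**4. Price of the corrected district version.** The critical value is 2.365 on 7 degrees of freedom. At school level, 60 schools less 8 district parameters and 1 treatment parameter leaves 51, with critical value 2.008. The ratio 2.365/2.008 = 1.18, so intervals are 18% wider for the same standard error. An effect with 80% power under a normal reference (noncentrality 1.960 + 0.842 = 2.802) has 67% power on 7 degrees of freedom and 78% on 51 (noncentral t, same standard error).

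**The case against.** The strongest reply is that the inflated error rate needs three things: clustering on district, a normal critical value, and no small-cluster correction. The article states at most the first. Critical values and corrections are commonly left to the full protocol or the analysis plan, neither of which is shown, so their absence is no fault. This stands, and the inflation can be stated only conditionally.

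Second, the sentence can be read as a loose summary of school-level clustering with district handled through the model terms. There would then be 60 clusters and the argument about 8 units would not apply. This reading is possible. It sits awkwardly, though, because district terms are covered in the preceding sentence and this one assigns district clustering to the robust errors. If it is what was meant, the reference to district should come out anyway.

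Third, much of the excess does not come from the clustering level. Like for like, uncorrected with a normal reference, district clustering gives about 10-14% and school clustering about 8-9%. This also stands: changing the level without adding a correction leaves most of the problem.

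Fourth, the simulations use a marginal Poisson model, not the planned mixed model, and an assumed intraclass correlation. Some datasets at the lowest rates were unusable. The figures are therefore approximate.

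**Conclusion.** The stated clustering level is a poor choice on the literal reading. Paired with a normal reference and no correction, it gives a two-sided type I error of about 9-14% for the pooled contrast. Paired with G/(G-1) and t(7), it is near nominal at about 4.5-6.5%, at a cost of about 18% in interval width (same standard error). Neither cost is required by a design that randomises schools within district strata.

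A reader might infer that this trial's true type I error is 9-12%, or that its intervals are certainly too narrow. The article does not support that, since it fixes neither the critical value nor the correction. Nor does it support saying that every primary interval is affected: the modelling text names contraceptive uptake and childbearing but not HIV testing. The effect on the facilitated-arm interval that sets the non-inferiority margin follows only if the same errors are used there, and it was not simulated.

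The figures rest on an assumed intraclass correlation of 0.01-0.05 and on the marginal model as a stand-in for the mixed model.

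**What to change.** In Data analysis, delete district from the robust-variance sentence and keep it as a stratification term. Account for clustering at school, by a school random intercept or school-clustered robust errors. In the analysis plan, name a small-sample correction and a t reference with about schools minus cluster-level parameters degrees of freedom (about 51 for the pooled contrast). This gives about 5-6% in the simulations. Both parts are needed. If district clustering is kept, state the reason, the correction and the 7 degrees of freedom, and accept the wider intervals.

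The cost is a short text change and intervals slightly wider than an uncorrected normal-based method would give; the critical value alone adds about 2% (2.008/1.960). No change to data collection or sample size is needed.
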